## Abstract

**Background:**

Spinal cord stimulation (SCS) is a surgical technique used in patients with chronic intractable pain, and its effectiveness and safety have been validated by multiple studies. However, to maintain an optimal and steady long-term effect is still challenging. Here, we report a new management paradigm integrating smartphone application and remote programming. Chronic pain patients with SCS implants can monitor their pain status on the phone and change stimulation parameters accordingly. The PreMaSy study is a randomized controlled trial to evaluate the clinical effectiveness and safety of this precise management system.

**Methods:**

Patients with chronic intractable pain will be screened for eligibility, and 82 participants are anticipated to be enrolled in this trial. After the electrode implantation, the stimulation effectiveness will be tested. Participants with a reduction of more than 50% in the visual analog scale (VAS) will receive implantation of an implantable pulse generator and randomized (1:1) into the experimental group or control group. All participants will be asked to take online follow-ups and complete assessments using a smartphone application. Daily pain characteristic assessments and monthly quality of life questionnaires are integrated into the App, and participants will be required to complete these assessments. The daily VAS for pain intensity will be monitored and a threshold will be set based on baseline VAS score. The interventional appointment will be scheduled once the threshold is reached. The primary outcome is the health condition and quality of life assessed by the five-level EuroQol five-dimensional questionnaire (EQ-5D-5L). Utility values of EQ-5D-5L will be assessed at baseline and 1, 3, and 6 months post-operative.

**Discussion:**

The PreMaSy study aims to evaluate the effectiveness and safety of a novel App-based, patient-centered, self-assessment management system for chronic intractable pain. A randomized controlled trial is designed to test the non-inferiority of this precise management system compared to the monthly online follow-ups. It is also expected to yield valuable experiences regarding precision medicine.

**Trial registration:**

ClinicalTrials.gov NCT05761392. Registered on March 07, 2023.

**Supplementary Information:**

The online version contains supplementary material available at 10.1186/s13063-023-07595-4.

## Introduction

As a growing public health concern, chronic pain has an impact on many aspects of patients’ lives. Not only does it affect physical functions and limit daily activities, but it also has a detrimental impact on work, social, and family-related consequences and decreases one’s quality of life [12]. Furthermore, it creates great medical and economic burdens. According to previous reports, the prevalence of chronic pain was approximately 20% in US adults [7] and over 30% in China [53]. The resulting economic burden is therefore enormous. It is estimated that the total cost of pain in the USA in 2008 was between 560 and 635 million dollars [15].

Spinal cord stimulation (SCS) is a technique that uses implanted electrodes to directly stimulate the dorsal columns of the spinal cord. It has been approved and widely used in a variety of pain control applications, for example, failed back surgery syndrome (FBSS) [42], complex regional pain syndrome [50], radiculopathy [51], and diabetic neuropathy [36, 37]. Favorable results were demonstrated by multiple clinical trials [20, 29], confirming the effectiveness of the therapy. However, there are certain hurdles that substantially hampered the real-world applications. First, it is recommended that stimulation paradigms be individualized and modified based on real-time patient feedback in order to maximize the efficacy [38]. Considering the electrode contacts and stimulation parameters such as current, voltage, and frequency, the number of all conceivable combinations is enormous. Second, significant fluctuations are reported in long-term implantations [41]. Thus, a long-term and extensive follow-up plan is often required to maintain a stable stimulation effect. Last but not the least, the disparity of medical service assessment should be taken into account. In China, for instance, only a few cities have qualified SCS-related clinics [23], and the COVID-19 pandemic has largely restricted travel between distant places, which has aggravated this disparity.

Attempts are being made to maintain maximum and stable efficacy with minimal financial and time expenditures by utilizing telemedicine and remote programming. Our group has reported for the first time the clinical application of remote programming for pain patients with a SCS implant using a video-based real-time remote programming system [32]. Our remote sessions allowed us to deliver remote programming operations accurately and safely, while reducing costs and providing convenience for patients.

But we wanted to take one step further. Pain characteristics differ not only across individuals but also within a single individual. For example, the pain intensity may change significantly throughout the day due to weather, mood, or sleep quality, or it may simply vary over time. But these shorter-term shifts are often ignored in both traditional and online programming sessions. Patients have to wait until scheduled follow-up sessions for major adjustments in stimulation parameters. A more precise application-based, patient-centered, self-assessment management scheme has been exploring in a broad range of diseases, for example, Parkinson’s disease [1], atrial fibrillation [17], and asthma [5].

Here, we introduce for the first time a precise management system for pain patients with a SCS implant, which combines self-assessment based on a customized smartphone application (App) and remote programming based on a remote and wireless programming system. In the proposed study, patients who use the precise management system will be compared to those who take conventional online follow-ups. We intend to investigate the effectiveness of this novel system and its application in a broader population.

## Methods

### Trial design

The PreMaSy study is a prospective, double-arm, enrichment-enrollment, randomized-controlled trial (Clinical trial registration ID: NCT05761392) designated to evaluate the effectiveness of the precise management system for chronic intractable pain. The precise management system is a novel App-based, patient-centered, self-assessment modality designed for patients who have chronic intractable pain and are treated with remote and wireless SCS. Compared with a classic RCT, an enrichment-enrollment trial increases the proportion of likely responders in order to maximize the differences between treatment and placebo effects, for example, in many analgetic drug trials [14, 39]. To enroll more “true” responders, the enrichment-enrollment trial shifts the randomization point, and in our instance, only after participants achieve at least a 50% reduction in pain intensity and tolerate SCS well during the test period.

The timeline of this study is divided into three distinct periods: (1) screen period, (2) test period, and (3) follow-up period (Fig. 1). Patients experiencing chronic intractable pain will be invited to participate in our study. After signing the informed consent, participants will be screened strictly for eligibility based on the inclusion and exclusion criteria (Tables 1 and 2). During the 2-week screen period, admission arrangements will be made and thorough pre-operative examinations will be administered. In addition to collecting basic information including demographics and present and historical medical history, baseline assessments including pain characteristics and quality of life will be documented as well (Fig. 2).

**Fig. 1 Fig1:**
[figure not shown]
Flow chart of the PreMaSy study

**Table 1 Tab1:** Inclusion criteria of the PreMaSy study

Inclusion criteria
1. Have been clinically diagnosed with chronic intractable pain for at least 3 months
2. Be unresponsive to or unsatisfied with conservative treatments, including but not limited to oral medication, nerve block, epidural corticosteroids, physical- and psychological rehabilitation therapy, and chiropractic care
3. At enrollment, aged 18 years or older
4. At enrollment, average pain intensity of at least 50 out of 100 mm on a visual analog scale
5. Be voluntary to take the trial and sign the informed consent
6. Have good compliance and ability to complete post-operative follow-ups
7. Have the basic ability to read and use a mobile phone or have a caregiver who can

**Table 2 Tab2:** Exclusion criteria of the PreMaSy study

Exclusion criteria
1. Have bleeding complications or coagulation disorders
2. Have mental or cognitive disorders leading to inability to complete implantation surgery or post-operative follow-up
3. Have issues with the spinal cord or vertebrates that are not suitable for implantation surgery
4. Have systemic active infections or local infections at the anticipated surgery area
5. Be pregnant, breast-feeding, plan to be pregnant, or unwilling to use contraceptive methods
6. Have metastatic tumors or untreated malignancies
7. Have a life expectancy of less than 1 year
8. Have already provided with a medication pump and/or other implanted devices
9. Require the use of MRI and/or thermo-therapy
10. Be heavily addicted to alcohol and/or drugs
11. Have an improvement in VAS of less than 50% or unable to tolerance SCS during the test period
12. Unable to complete long-term online follow-ups because of hardware issues such as internet, mobile phones, and so on

**Fig. 2 Fig2:**
[figure not shown]
Standard Protocol Items: Recommendations for Interventional Trials (SPIRIT) figure

Participants will then undertake the SCS electrode implantation and enter the 10-day (± 4) test period. Pain intensity will be monitored during this time. Only participants who have an improvement of no less than 50% in visual analog scale (VAS) will undertake the implantable pulse generator (IPG) implantation. After the IPG implantation, participants will be randomized (1:1) into one of the two groups: the experimental group (EG) with PreMaSy or the control group (CG) with conventional follow-ups. The randomization will be generated by computers and concealed from the recruitment team and data analysis team. The participants and their physicians, however, will not be blinded from their own randomization results, because the consequent assessments are dependent on which group they are in. The detailed assessments of the two groups are shown in Fig. 2. Participants in CG will take follow-ups only at 1, 3, and 6 months post-operative, while participants in EG will take additional monthly quality of life assessments and daily pain characteristics assessments, which can be done in a customized App. These results will be automatically monitored and timely interventional appointment will be scheduled whenever the intervention threshold is reached.

The PreMaSy study protocol was written in accordance with the Standard Protocol Items: Recommendations for Interventional Trials Statement (SPIRIT). A SPIRIT checklist is included in Additional file 1. The trial will be carried out according to the principles of the Declaration of Helsinki (Edinburgh version, 2000).

### Participants

#### Study population

The study will be primarily conducted in the Neurosurgery Center of Beijing Tsinghua Changgung Hospital. Additional centers may be added as the study progresses. The protocol has been approved by the Clinical Trial Ethics Committee of Beijing Tsinghua Changgung Hospital (approval number: 22442–4-02). It is anticipated that the enrollment will end prior to September 2024. And invitations will be sent to our clinic patients experiencing chronic intractable pain during that time.

#### Inclusion criteria

The inclusion criteria are shown in Table 1.

#### Exclusion criteria

The exclusion criteria are shown in Table 2.

### App design

Our research team in cooperation with Beijing Pinchi Software Development Co., Ltd. developed an App that integrates the wireless control of the stimulation device and the follow-up assessments. The App can connect wirelessly to the IPG device based on our previously developed remote and wireless SCS system [32]. Four sets of personalized stimulation parameters will be programmed to optimize the analgesic effect and stored in the App before participants are discharged. Participants will be given complete control over the stimulation, including turning it on and off and changing the parameter set in use according to their preferences.

The assessment module was designed as a crucial element in the precise management system. Four major sections are included: (1) daily assessments, (2) monthly assessments, (3) hardware-related issues, and (4) satisfaction with App usage.

The daily assessment section primarily focuses on the evaluation of multiple pain characteristics, including intensity, temporal, and spatial features. Pain intensity is measured by a VAS slider customized to mobile phone screen size (Fig. 3A) [44]. To measure the temporal features, we designed a hand-drawn time-intensity curve (Fig. 3B). The *x*-axis of the curve represents 24 h in a day, while the *y*-axis represents the VAS score of pain intensity. The participants are asked to recall their pain experience from the previous day and draw a curve to depict the fluctuations in pain intensity over time. As for the spatial features, we referred to the pain area drawing in the Brief Pain Inventory (BPI) and designed a version that is touch-screen compatible. In order to standardize the pain map, the front and rear body projections were separated according to the dermatome pattern. However, the pattern was too detailed to be identified accurately on a smartphone display. Therefore, we consolidated certain consecutive dermatomes and generated 25 gross selection areas (Fig. 3C, D).

**Fig. 3 Fig3:**
[figure not shown]
The daily assessments designed for the App. **A** Slider of VAS for general pain intensity. The current position indicates 5.0 out of 10.0. **B** Time-intensity curve for pain temporal characteristics. The *x*-axis depicts 24 h in a day in 3-h increments, and the *y*-axis depicts the pain intensity. The red curve simulates a patient’s hand-drawn curve. **C**, **D** Simplified pain map based on the dermatome pattern. There are a total of 25 pairs of body area presented, including 12 front (**C**) and 13 back (**D**). The indicators highlighted in blue simulate selections from an imaginative candidate

The monthly assessment section, on the other hand, focuses on the long-term pain-related quality of life. The Five-Level EuroQol Five-Dimensional Questionnaire (EQ-5D-5L) is a widely used instrument for assessing general health that consists of mobility, self-care, usual activities, pain/discomfort, and anxiety/depression [21]. We used the published value set for China to evaluate various health statuses [34]. The EQ-VAS is used as well for the global health condition. Sleep quality is assessed by the Pittsburgh Sleep Quality Index (PSQI) with 18 items covering seven categories [4]. Patients’ Global Impression of Change (PGIC) and Clinical Global Impressions-Improvements (CGI-I) are two seven-level questionnaires that measure the perceptions of the improvements in the participants’ overall health conditions, respectively from their own [45] and their physicians [3].

Impedance tests, parameter adjustments, adverse events (AEs), and other hardware-related issues are collected. Participants and their physicians are also asked to take satisfaction surveys based on their App usage experiences and encouraged to provide feedback. All aforementioned assessment modules will be activated automatically when the profile of a participant is established, and in order to enhance compliance, notifications of incomplete assessments will be sent at a set time.

### Interventions

During the test period, electrode implantation and IPG implantation will be undertaken in patients who qualify. After surgery, stimulation parameters will be optimized for analgesia. In our prior work, we have described the implantation surgery, stimulation device, and programming procedure in detail [31]. The aforementioned App will be utilized for subsequent follow-ups and pain management. Upon enrollment, an App account will be assigned to each participant. They will be instructed to activate the account and fill up the profile. As soon as they undergo the implantation procedure and are randomly assigned to either EG or CG, the App will only display contents exclusively to their group.

For participants in CG, they will be scheduled for follow-ups at conventional intervals, i.e., 1, 3, and 6 months post-operative. They can only access monthly assessments during the corresponding months. For participants in EG, on the other hand, the precise management system will be implemented. In addition to the standard follow-ups, they will be asked to complete every monthly assessment throughout the 6-month follow-up period. They will have access to the daily assessments in which they will be instructed to record and track their pain characteristics. Pain intensity VAS data collected after the electrode implantation and prior to the IPG implantation will be averaged and served as the baseline. The interventional threshold will be a minimum clinically significant difference (MCSD) of 20 mm (out of 100 mm VAS) [27] added to the baseline value. The system will monitor each participant’s daily VAS score automatically. If the score surpasses the threshold three times in a row, an alarm will be sent to their physicians and a remote programming appointment will be scheduled.

To improve adherence, the background system will monitor the assessments’ completion status, and specialists will be allocated to inquire about the incompletion. Other concomitant care including medications are only permitted by approval of investigators. Both CG and EG participants have the same access to report hardware-related issues and satisfaction with App usage. In the case of adverse events (AEs) or unexpected worsening, they may also schedule an urgent appointment.

### Outcomes

#### Primary outcome

As previously stated, EQ-5D-5L is a questionnaire which measures five dimensions. It depicts different health conditions as five-digit numbers corresponding to unique utility values. The primary outcome of the PreMaSy study is the change of EQ-5D-5L utility values between CG and EG at the 6-month follow-up compared to baseline values. After passing the eligibility screening, they will be required to fill up an EQ-5Q-5L questionnaire based on their pain experience prior to enrollment, and this value will serve as the baseline. The primary outcome formula is:$$\left({\mathrm{EQ}}_{\mathrm{EG}6}-{\mathrm{EQ}}_{\mathrm{EGbase}}\right)-\left({\mathrm{EQ}}_{\mathrm{CG}6}-{\mathrm{EQ}}_{\mathrm{CGbase}}\right)$$

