### Statistical methods

#### Sample size

The primary comparison in this study is the difference between EG and CG in quality of life score measuring by EQ-5D-5L. The EQ-5D-5L difference is assumed to be 0.53 with a standard deviation (SD) of 0.69 based on previous studies into the effectiveness of App-based therapy for chronic pain [40]. A sample size of 82 (41 per group) is calculated by the following formula:$$n=\frac{(1+r){({Z}_{\alpha }+{Z}_{1-\beta })}^{2}{\sigma }^{2}}{r{(\left|D\right|+\Delta )}^{2}}$$

$$Z$$ is the quantile of the standard normal distribution, $$\alpha$$ is the first-class error level, $$\beta$$ is the second-class error level for the statistical test, and $$r$$ is the allocation ratio, which is 1:1 in this equal allocation trial. Here, to detect the significant difference at a significant level of 0.05 with 80% power using a two-tailed* t* test, $${Z}_{\alpha }$$ and $${Z}_{1-\beta }$$ are determined as 1.96 ($$\alpha$$ = 0.05) and 0.84 ($$\beta$$ = 0.2), respectively. $$\sigma$$ is the expected SD of the outcome, and $$\left|D\right|$$ is the expected mean difference of the two groups. The non-inferiority limit is set at 10% [10], and $$\Delta$$ is 0.053. The sample size per group is calculated with the above formula, and the given value is 22. With the assumption of a 60% “true” responding rate and a 10% possible attrition rate, the final calculation of the sample size is 41 pairs ($$N$$ = 82).

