#### Primary and additional analyses

The primary effectiveness analysis is the 6-month non-inferiority of the within-group difference between CG and EG for the overall health-related quality of life measured by EQ-5D-5L. Non-inferiority will be tested between the two groups at a one-sided significance of 0.05, and if the non-inferiority of the primary endpoint was achieved, superiority will be tested at a one-sided significance of 0.025.

For secondary endpoints, non-inferiority will be also tested with a 10% non-inferiority margin and a one-sided significance of 0.05. Secondary endpoints include changes from baseline of EQ-5D-5L scores in 1 and 3 months, VAS scores, time-intensity curves, pain map, EQ-VAS scores, PSQI, PGIC, CGI-I, and satisfaction with App usage. Continuous variables will be summarized using means and standard error, and categorical variables will be summarized using frequency distributions. Parametric tests (e.g., *t* test and ANOVA) will be performed with data of normal distributions. Non-parametric tests (e.g., Wilcoxon rank-sum test and Mann–Whitney test) will be performed if parametric tests are not indicated. All statistical analyses will be performed in a validated statistical software package (e.g., SAS or SPSS).

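### The primary EQ-5D-5L comparison is set out as an unadjusted difference of changes; adjusting for baseline utility needs only wording and may gain precision, by an amount the article does not let us fix

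*Protocol article*

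**What the plan says.** Under Primary outcome, the protocol article gives the endpoint as "the change of EQ-5D-5L utility values between CG and EG at the 6-month follow-up compared to baseline values". The sentence beginning "The primary outcome formula is" then sets it out as (EG at 6 months minus EG baseline) minus (CG at 6 months minus CG baseline), with no covariate. The baseline questionnaire is completed after eligibility screening and is answered "based on their pain experience prior to enrollment, and this value will serve as the baseline". It therefore precedes electrode implantation, the test period and randomisation.

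Under Sample size, the trial is planned "to detect the significant difference at a significant level of 0.05 with 80% power using a two-tailed" t test. The input is: "The EQ-5D-5L difference is assumed to be 0.53 with a standard deviation (SD) of 0.69".

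Under Primary and additional analyses, the article states: "The primary effectiveness analysis is the 6-month non-inferiority of the within-group difference between CG and EG". A later sentence, after the list of secondary endpoints, says that parametric tests "will be performed with data of normal distributions". It gives the t test and ANOVA as examples, with rank tests as the fallback. The article nowhere mentions ANCOVA, adjustment for baseline or a repeated-measures model. EQ-5D-5L is collected at 1, 3 and 6 months in both arms; the 1- and 3-month values are secondary outcomes.

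**The concern.** Subtracting the whole baseline from the 6-month value fixes the regression slope on baseline at 1. A lower slope is plausible in this trial. The baseline is partly recalled. Implantation, a test period and selection on at least 50% VAS improvement come between it and randomisation, and the outcome is measured months later under stimulation. If the true slope is below 1, the change score over-corrects for any chance baseline imbalance between the arms. That error averages to zero over randomisations, but it adds variance.

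What is at stake is the width of the confidence interval in a small trial. The baseline utility that could narrow it is already collected from every participant before randomisation.

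**Working it through.** **Inputs from the Sample size section.** D = 0.53, SD = 0.69, margin = 0.053, Z values 1.96 and 0.84, allocation 1:1, responding rate 60%, attrition 10%.

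**The plan's own figure.** n per group = 2 × (1.96 + 0.84)² × 0.69² / (0.53 + 0.053)² = 21.96, so 22. Inflated: 22 / 0.6 / 0.9 = 40.74, so 41. Both stated figures reproduce.

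**Variance comparison.** Let the 6-month SD be s, the baseline SD be k × s, and the baseline to 6-month correlation be rho. The article gives neither k nor rho, so both are assumed below.

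- Change score: s² × (1 + k² − 2 × rho × k)
- Baseline-adjusted (ANCOVA, large samples): s² × (1 − rho²)
- Difference between the two: s² × (k − rho)², which is never negative and is zero when k = rho

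With equal SDs (k = 1), the ratio of adjusted to change-score variance reduces to (1 + rho)/2. Results at rho 0.3, 0.5 and 0.7:

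| SD ratio k | rho 0.3 | rho 0.5 | rho 0.7 |
|---|---|---|---|
| 0.5 | 0.958 | 1.000 | 0.927 |
| 0.75 | 0.818 | 0.923 | 0.995 |
| 1 | 0.650 | 0.750 | 0.850 |
| 1.25 | 0.502 | 0.571 | 0.628 |
| 1.5 | 0.387 | 0.429 | 0.443 |

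At k = 0.7 and rho 0.5: 0.75 / (1 + 0.49 − 0.70) = 0.75 / 0.79 = 0.95. At k = 0.7 and rho 0.3: 0.91 / (1 + 0.49 − 0.42) = 0.91 / 1.07 = 0.85.

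**What this means on the plan's inputs.** Take 0.69 as the SD of the change, and k = 1.

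- The standard error falls by 1 − √0.65 = 19%, 1 − √0.75 = 13% or 1 − √0.85 = 8%.
- At 22 per group and Z = 1.96, the unadjusted SE is 0.69 × √(2/22) = 0.208. Power is Φ(0.583/0.208 − 1.96) = 80%. With the SE reduced as above, it is 93.5%, 89.9% or 86.0%.
- The effective size of 22 per group becomes 22/0.65 = 33.8, 22/0.75 = 29.3 or 22/0.85 = 25.9. These figures hold only for equal SDs.

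If 0.69 is instead the SD of the 6-month score (k = 1), the change-score requirement is 21.96 × 2(1 − rho) = 30.7, 22.0 or 13.2 per group. The adjusted requirement is 21.96 × (1 − rho²) = 20.0, 16.5 or 11.2.

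**Does it help the non-inferiority test when the arms are truly equal?** Take 41 × 0.9 = 36.9 evaluable per arm and the one-sided 0.05 of the analysis section ("Non-inferiority will be tested between the two groups at a one-sided significance of 0.05"). The unadjusted SE is 0.69 × √(2/36.9) = 0.161, and power is Φ(0.053/0.161 − 1.645) = 9.4%. With adjustment at rho 0.5 and k = 1, the SE is 0.139 and power is 10.3%. The difference between Z = 1.96 in the sample size and one-sided 0.05 in the analysis is a separate matter.

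**The case against.** The strongest reply is that the article does not fix the estimator. The tests under Primary and additional analyses are examples, the paragraph on the primary endpoint names none, and the t test elsewhere only supports the sample size. The formula can be read as defining the outcome, and a baseline-adjusted model targets the same quantity. Covariates are commonly left to the SAP, which is not shown. This stands in part: an adjusted model may already exist there. But the formula is printed without a covariate and every named test is unadjusted, so the point concerns what is stated.

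Four stronger readings are tempting, and the document supports none of them:

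- **That the planned analysis is biased or invalid.** It is not; under randomisation the raw contrast is unbiased.
- **That the trial is underpowered because of it.** The sample-size section describes sigma as the SD expected for the outcome, and the outcome is the change. On that reading, the 80% was planned for the unadjusted analysis, and adjustment is a bonus.
- **That the gain is known to be 15% to 35% of the variance.** That range needs equal SDs. Entry requires a VAS of at least 50 mm, which may narrow baseline health status, and a smaller baseline SD can remove most or all of the gain.
- **That the narrow margin makes adjustment decisive, or that a repeated-measures model is required.** Power at a true difference of 0 hardly moves. Treating months 1 and 3 as secondary is legitimate, those visits add little to the month-6 contrast when data are complete, and their value for missing month-6 data rests on missing-data assumptions.

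**Conclusion.** The point holds as a possible loss of efficiency. The contrast as printed is valid but forces a slope of 1, and baseline adjustment estimates the same between-group difference with a large-sample variance that is never higher.

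The size depends on rho and the SD ratio, both assumed here. Across the values tabulated, the gain runs from nil (SD ratio equal to rho) to more than half the variance (baseline SD 1.5 times the 6-month SD). The equal-SD case gives 35%, 25% or 15% at rho 0.3, 0.5 or 0.7. The never-higher statement is a large-sample one; in a trial this small, estimating the slope has a minor cost.

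This is a near-free improvement. It is no remedy for the low non-inferiority power at a true difference of 0, which comes from the margin and the assumed effect.

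**What to change.** Keep the outcome definition and its formula. Add one sentence on estimation: the EG minus CG difference in EQ-5D-5L utility at 6 months will be estimated from a linear model with treatment group and baseline EQ-5D-5L utility, and its confidence interval will be compared with the non-inferiority margin and then with 0. Name the raw difference of mean changes as a supportive analysis.

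A repeated-measures model on the 1-, 3- and 6-month visits common to both arms is optional. It could retain participants who miss month 6 but have earlier values.

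If the SAP already specifies a baseline-adjusted model, it is enough to align the two documents. The cost is wording only: no new data, visits or participants. The choice should be recorded before anyone compares outcomes by arm, so that it cannot be made on the results.

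### The primary change score starts from a pre-implant EQ-5D-5L and no on-stimulation EQ-5D-5L is described before randomisation, which costs precision and hides early loss of benefit but does not bias the comparison

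*Protocol article*

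**What the plan says.** The Primary outcome section defines the endpoint as "the change of EQ-5D-5L utility values between CG and EG at the 6-month follow-up compared to baseline values". It writes this as a formula: the EG change minus the CG change. The baseline is completed once eligibility screening is passed; patients are "required to fill up an EQ-5Q-5L questionnaire based on their pain experience prior to enrollment, and this value will serve as the baseline". Trial design likewise places it in the screen period, where "baseline assessments including pain characteristics and quality of life will be documented as well".

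Several steps then come before allocation. Patients have the electrode implanted and "enter the 10-day (± 4) test period. Pain intensity will be monitored during this time". Trial design says that the randomisation point is shifted, in this trial to "only after participants achieve at least a 50% reduction in pain intensity and tolerate SCS well during the test period". The text after Figure 2 adds: "After the IPG implantation, participants will be randomized (1:1) into one of the two groups".

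The Abstract (Methods) gives the measurement times: "Utility values of EQ-5D-5L will be assessed at baseline and 1, 3, and 6 months post-operative". None of these falls between the pre-implant baseline and month 1.

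Pain is handled differently. Under Interventions, "Pain intensity VAS data collected after the electrode implantation and prior to the IPG implantation will be averaged and served as the baseline", and this value sets the alarm threshold. Figure 2, the assessment schedule, is not available in the text under review.

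**The concern.** Everyone randomised has already responded to stimulation. The arms differ only in how that response is managed afterwards. The primary change score nevertheless runs from before the implant to month 6, so each patient's change contains that patient's own response to stimulation as well as anything due to management. How much a patient gained from stimulation before allocation tells us nothing about the management system, and for this comparison its variation is noise.

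Two things are at stake. The first is precision, in a trial whose non-inferiority margin is only 0.053. The second is interpretation. The Discussion names sustaining efficacy as one of the problems in the field, but without a utility value on stimulation before the arms diverge, any benefit lost between randomisation and month 1 cannot be seen on the primary scale.

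**Working it through.** **1. The plan's own figure.** Inputs from Sample size: difference 0.53, SD 0.69, margin 0.053, Z values 1.96 and 0.84, allocation 1:1.

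n = 2 × (1.96 + 0.84)² × 0.69² / (0.53 + 0.053)² = 7.465 / 0.3399 = 21.96, so 22 per group.

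22 / 0.6 / 0.9 = 40.7, so 41 per group and N = 82. The stated figures reproduce, and this point does not change them.

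**2. Is the contrast biased?** Let S be the mean stimulation effect common to both arms and M the management effect. The stated formula has expectation (S + M) - S = M, so S cancels. A simulation of 20,000 trials with 41 per arm and an assumed M of 0.05 agrees. For S = 0, 0.2 and 0.4 the mean estimate is 0.050, 0.049 and 0.050 with the pre-implant baseline, and 0.050 each time with a randomisation-time baseline.

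**3. What stays in the variance.** The simulation assumes these SDs: individual stimulation response 0.15, further change before randomisation 0.05, later change 0.10.

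- Pre-implant baseline: change variance = 0.0225 + 0.0025 + 0.0100 = 0.035; SE = √(2 × 0.035 / 41) = 0.041.
- Randomisation-time baseline: change variance = 0.0100; SE = √(2 × 0.010 / 41) = 0.022.

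This favours the added score, because it lets the pre-randomisation value carry through to month 6 with no post-surgical disturbance. It shows the mechanism and does not forecast the gain.

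**4. General dependence on correlation.** Let rho be the correlation between a baseline and the 6-month value, with equal variances at the two times. The article does not give rho. Variances are relative to the 6-month value alone.

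| rho | raw change, 2(1 - rho) | ANCOVA, 1 - rho² | ratio, 2/(1 + rho) |
|---|---|---|---|
| 0 | 2.00 | 1.00 | 2.00 |
| 0.2 | 1.60 | 0.96 | 1.67 |
| 0.3 | 1.40 | 0.91 | 1.54 |
| 0.5 | 1.00 | 0.75 | 1.33 |
| 0.6 | 0.80 | 0.64 | 1.25 |
| 0.7 | 0.60 | 0.51 | 1.18 |
| 0.8 | 0.40 | 0.36 | 1.11 |

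Below rho = 0.5 the raw change is noisier than ignoring the baseline altogether. At every rho shown ANCOVA is the more precise of the two.

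**5. Splitting the gain.** Assume rho = 0.3 for the pre-implant score and 0.6 for an on-stimulation score. Adjusting for the existing baseline takes the variance from 1.40 to 0.91, a cut of 35%. Adjusting for the on-stimulation score as well brings it to 0.64 or lower, a further cut of about 30% (0.64 / 0.91 = 0.70).

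**6. Scale against the margin.** Assume that 0.69 is the SD of the change score (the article does not say) and that all 41 per arm are analysed. Then SE = 0.69 × √(2/41) = 0.152, and the one-sided 95% half-width is 1.645 × 0.152 = 0.25, nearly five times 0.053. At rho = 0.3, ANCOVA on the existing baseline gives 0.152 × √(0.91/1.40) = 0.123. With a second covariate at 0.6 the SE is at most 0.152 × √(0.64/1.40) = 0.103.

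**The case against.** The strongest reply is that a pre-treatment baseline is a legitimate choice. The stated objective is non-inferiority on 6-month quality of life, not maintenance from an on-stimulation level, and randomisation makes the contrast valid whichever baseline is used. That stands: there is no error or contradiction in the choice itself.

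A reader might also infer more than the documents support:

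- *That the stimulation effect is confounded with the management effect.* It is not. The common effect cancels in the stated formula, as does any recall error unrelated to arm.
- *That nothing is measured around randomisation.* Pain VAS on trial stimulation is averaged shortly before it. Only EQ-5D-5L is not described, and Figure 2 cannot be checked.
- *That the baseline and follow-up scores have different recall periods.* The article gives no recall wording for the follow-ups. For patients with at least 3 months of intractable pain, a form filled in before the implant may well describe their current state.
- *That the trial cannot detect loss of benefit.* Scores at months 1, 3 and 6 in both arms show later loss. Only loss before month 1 is hidden.

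The gain from the extra score is also uncertain. A score taken close to surgery could correlate poorly with month 6, and selecting responders narrows its range. At the assumed rho of 0.3, adjusting for the existing baseline already gives more than the new score adds, and covariate adjustment is often left to an analysis plan. That limits the point but does not remove it, because the article itself writes the primary outcome as an unadjusted difference of changes.

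**Conclusion.** The point holds as one of precision and interpretability, not of validity. As written, the primary outcome keeps between-patient variation in stimulation response as noise, and the text shown offers no utility value at the start of randomised follow-up. For rho from 0 to 0.8, the raw change has 2.0 to 1.1 times the variance of an analysis adjusted for the same baseline. That range assumes equal variances at the two times.

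The further gain from an on-stimulation score is about 30% of the remaining variance if the correlations are 0.3 and 0.6. It could be small or nil, since neither correlation is documented. N = 82 is unaffected. The statement that no EQ-5D-5L is taken before allocation rests on the text alone and should be checked against Figure 2.

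**What to change.** 1. Keep the pre-implant EQ-5D-5L as the baseline, so that total benefit from stimulation can still be described.
2. Add one EQ-5D-5L in the App after the test period and before the allocation is released. The order matters: the trial is open, so a score given after the patient knows the arm is no longer a baseline covariate.
3. Compare 6-month utility between arms by ANCOVA, adjusting for the pre-implant value and, where available, the pre-randomisation value, in place of the raw difference of changes. The quantity estimated is still the between-arm difference in 6-month utility, so the margin stays on the same scale.
4. For patients already enrolled, who will lack the new score, state in advance either a missing indicator or imputation of the baseline covariate.

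The cost is one five-item questionnaire during the hospital stay and a short change to the primary outcome text. The added score may carry short-term post-surgical discomfort, expected equally in both arms. Recruitment began in September 2022, so the score will be missing for those already enrolled. If the team does not want a new assessment, the ANCOVA on the existing baseline needs no new data and secures the more certain part of the gain.
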